**Methods:**

This prospective study aims to include patients for whom ^131^I-therapy is indicated as part of the treatment for differentiated thyroid cancer in a Paris hospital (40 and 80 patients in the 1.1 GBq and 3.7 GBq groups, respectively). The follow-up is based on three scheduled visits: at inclusion (T0, immediately before ^131^I-therapy), and at 6 months (T6) and 18 months (T18) posttreatment. For each visit, questionnaires on salivary dysfunctions (validated French tool), quality of life (Hospital Anxiety and Depression scale, Medical Outcomes Study 36-Item Short Form Survey), and nutritional status (visual analog scale) are administered by a trained clinical research associate. At T0 and T6, saliva samples and individual measurements of the salivary flow, without and with salivary glands stimulation, are performed. External thermoluminescent dosimeters are positioned on the skin opposite the salivary glands and at the sternal fork immediately before ^131^I administration and removed after 5 days. From the doses recorded by the dosimeters, an estimation of the dose received at the salivary glands will be carried out using physical and computational phantoms. Genetic and epigenetic analyses will be performed to search for potential biomarkers of the predisposition to develop salivary dysfunctions after ^131^I-therapy.

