#### Secondary Endpoints

Secondary endpoints are defined as follows: change in quality-of-life score between T0, T6, and T18; change in nutrition between T0, T6, and T18; change in chemical saliva composition between T0 and T6; change in anxiety and depression symptoms between T0, T6, and T18; genetic and/or epigenetic variant identification that may modify the risk of salivary dysfunctions after ^131^I-therapy; identification of individual factors associated with salivary dysfunctions at T6 and T18; and dose-response analysis between the ^131^I-dose received precisely at the salivary glands and salivary dysfunctions at T6 and T18.

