#### Planned Analyses

Paired comparison tests will be used to assess differences in data between T0 and T6. Correlations, principal component analyses, and multiple correspondence analyses will be used to study the factors (objective and subjective) common to patients with salivary dysfunctions after ^131^I-therapy.

All factors significant at a 10% threshold in univariate analyses using different regression models (Textbox 1) will then be entered into multivariate models to measure the risk of developing salivary dysfunctions or other outcomes, adjusted for risk factors previously identified.

The mixed regression models, adjusted for confounders, performed to investigate the temporal evolution for the different outcomes, will be set up using a random intercept for each patient with a first-order autoregressive covariance structure to account for repeated measurements.

The different scores to the questionnaires for quality of life, nutrition, and symptoms of depression and anxiety assessments are calculated and classes are created according to the recommendations for each questionnaire and for each visit (T0, T6, and T18).

Synthesis of the planned analyses.

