**Outcomes**
CategoricalDry mouth sensation after treatment, dry eye (Ocular Surface Disease Index), Hospital Anxiety and Depression (HAD) anxiety scale, HAD depression scale, changes in nutrition, composite outcome (sum of dysfunctions)ContinuousUnstimulated saliva flow (mL/min), stimulated saliva flow (mL/min), saliva pH, electrolyte concentrations in saliva (mmol/L), physical composite score (Medical Outcome Study Short Form 36 items [MOS SF-36]), mental composite score (MOS SF-36), genetic and/or epigenetic variants

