**Models and tests**
Categorical*χ*^2^, logistic regression, Poisson regressionContinuousCorrelations, *t* test, linear regressions, mixed model

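### HAD and OSDI scores are listed as categorical outcomes, and Textbox 1 and the Planned Analyses text disagree on which repeated-measures model covers change in anxiety and depression to T18

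*Protocol article*

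**What the plan says.** Under Planned Analyses, the scores for quality of life, nutrition, depression and anxiety are computed and "classes are created according to the recommendations for each questionnaire and for each visit". The outcomes list in Textbox 1 then places these among the categorical outcomes: "dry eye (Ocular Surface Disease Index), Hospital Anxiety and Depression (HAD) anxiety scale, HAD depression scale, changes in nutrition". The SF-36 physical and mental composites are in the continuous list. Table 1 draws the same line, with OSDI, nutrition and HAD under qualitative data and only the SF-36 composites under quantitative data.

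The models list in Textbox 1 gives categorical outcomes the chi-square test, logistic regression and Poisson regression. The continuous list ends with "linear regressions, mixed model", and the mixed model appears nowhere else in the textbox.

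The Planned Analyses text is wider. It states "Paired comparison tests will be used to assess differences in data between T0 and T6", and it says that mixed regression models, "performed to investigate the temporal evolution for the different outcomes, will be set up using a random intercept for each patient", carry a first-order autoregressive structure for the repeated measurements. Neither sentence is restricted to continuous outcomes.

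The Secondary Endpoints section includes "change in anxiety and depression symptoms between T0, T6, and T18", and change in nutrition over the same visits. The abstract describes the nutrition measure as "nutritional status (visual analog scale").

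**The concern.** Two things are at stake.

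The first is precision. A change in score that does not cross a cut-point disappears once the score is classed. Where most patients sit in the lowest class, as they do for depression and dry eye at baseline, little of the score's information survives. The article gives no reason for keeping SF-36 continuous while classing HAD and OSDI.

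The second is which model will be run. A three-visit change endpoint needs a method that allows for repeated measurements on the same patient. For the classed HAD outcomes the textbox lists none, while the section text seems to supply one. An analyst following the textbox and one following the text would do different analyses of the same secondary endpoint.

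**Working it through.** **1. Passages side by side**

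| Question | Planned Analyses text | Textbox 1 |
|---|---|---|
| Form of HAD outcomes | scores calculated, then classed | categorical |
| Form of OSDI | not named in the scoring sentence | categorical |
| Form of SF-36 composites | scores calculated, then classed | continuous |
| T0 to T6 comparison | paired tests, all data | pairing not marked in either row |
| Change through T18 | mixed models for the outcomes in general | mixed model in the continuous row only |

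For the classed HAD outcomes, the only text that reaches T18 is the mixed-model sentence, and the textbox does not assign that model to them. Textbox and text therefore conflict on this endpoint.

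**2. Size of the loss from classing**

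The plan has no figure of its own to reproduce here. Its sample size concerns salivary dysfunction rates and does not bear on this point.

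Inputs, all at T0:
- Depression, suspicious or obvious (Results): 19/139 = 0.1367 (printed as 13.6%).
- Anxiety, suspicious or obvious (Results): 67/139 = 0.4820.
- OSDI (Table 2): 112 normal, 11 light, 6 mild, 5 severe, total 134, so 22/134 = 0.1642 are not normal.

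Assumption: the underlying score is normal.

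*Two classes.* The efficiency relative to the continuous score is φ(z_p)² / [p(1 − p)], where z_p cuts off the upper share p.
- Depression: z = 1.095, φ = 0.2190; 0.04795 / 0.11801 = 0.406, a loss of 59.4%.
- OSDI: z = 0.977, φ = 0.2474; 0.06122 / 0.13722 = 0.446, a loss of 55.4%.
- Anxiety: z = 0.045, φ = 0.3985; 0.15883 / 0.24968 = 0.636, a loss of 36.4%.

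*Ordered classes kept.* The efficiency is the sum over classes of (φ_lower − φ_upper)² / p_class.
- OSDI, four classes: φ at the three cuts is 0.2474, 0.1516 and 0.0814. The terms are 0.0732 + 0.1119 + 0.1099 + 0.1777 = 0.473, a loss of 52.7%.
- HAD, three classes: the article pools the upper two, so I assumed that they split from 30:70 to 70:30.
  - Depression: efficiency 0.416 to 0.424, a loss of 57.6-58.4%.
  - Anxiety: efficiency 0.710 to 0.751, a loss of 24.9-29.0%.

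| Score | Loss, two classes | Loss, ordered classes kept |
|---|---|---|
| Depression | 59% | 58% |
| OSDI | 55% | 53% |
| Anxiety | 36% | 25-29% |

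More classes help anxiety but barely help depression or OSDI, because most patients fall in the lowest class.

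**3. What cannot be computed**

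These are cross-sectional figures at T0. The loss for within-patient change would need the correlation between visits and the class shares at T6 and T18, and the article gives neither. No class shares are given for nutrition.

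**The case against.** A reader might infer from the textbox that these outcomes get only unpaired tests, so that visits are treated as independent and the standard errors are wrong. The article does not support that. It plans paired tests from T0 to T6 and random-intercept models, neither limited to continuous outcomes. The textbox is a synthesis, it marks no pairing in the continuous row either, and mixed regression can be logistic. For questions at a single visit its categorical methods are valid. What remains is the disagreement over change through T18.

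A reader might also take 59% as the information lost on the change endpoints. It is the worst case: depression alone, two classes, a normal score at one visit. The article does not say that two classes will be used; its wording for HAD implies at least three, and Table 2 shows four for OSDI.

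Dry eye might be read as one of the secondary change endpoints. It is not; eye dryness is a component of the primary composite at T6. OSDI belongs here only as a classed outcome in Textbox 1.

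The best case for the plan is that instrument classes are clinically interpretable and that creating them does not prove the scores are dropped, since the scoring sentence also covers quality of life, whose composites stay continuous. The first part stands, and supports reporting the classes. The second is weakened by the rest of the article: Table 1, the Results and Table 2 show HAD and OSDI only as classes or qualitative data, and no continuous analysis of either is mentioned.

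The doubt over nutrition stands. Only the abstract calls it a visual analog scale, Table 1 treats it as qualitative, and the Results report items such as drinking more often. The questionnaire appendix is not shown.

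**Conclusion.** The point holds as a cheap improvement. HAD anxiety, HAD depression and OSDI are listed as categorical although numeric scores underlie them, and Textbox 1 conflicts with the Planned Analyses text on the model for change in anxiety and depression across T0, T6 and T18. Classing costs about 58-59% of the cross-sectional information for depression, 53-55% for OSDI and 25-36% for anxiety. These ranges rest on a normal underlying score, the baseline class shares and, for three-class HAD, an assumed split of the upper classes. Normality is least safe for scores that may be skewed, such as OSDI. The point does not show that the planned standard errors are wrong, and it gives no figure for the loss on within-patient change or on nutrition.

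**What to change.** Move the HAD anxiety, HAD depression and OSDI scores to the continuous row of Textbox 1 and analyse them with the repeated-measures mixed model already planned. Do the same for nutrition if the instrument is in fact a numeric visual analog scale. Keep the instrument classes for description. Where a class is itself compared over visits, name a repeated-measures categorical model (GEE or mixed logistic) in the categorical row, so that textbox and text agree.

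The cost is a change of wording: HAD scores are already calculated, and OSDI classes presuppose a score. No data collection or sample size changes, and T18 follow-up was still underway at publication. The small downside is that skewed scores may need a transformation or robust standard errors.

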**Outcomes**
CategoricalDry mouth sensation after treatment, dry eye (Ocular Surface Disease Index), Hospital Anxiety and Depression (HAD) anxiety scale, HAD depression scale, changes in nutrition, composite outcome (sum of dysfunctions)ContinuousUnstimulated saliva flow (mL/min), stimulated saliva flow (mL/min), saliva pH, electrolyte concentrations in saliva (mmol/L), physical composite score (Medical Outcome Study Short Form 36 items [MOS SF-36]), mental composite score (MOS SF-36), genetic and/or epigenetic variants

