Finally, while a strong interrelationship between epigenetic processes and genetic factors associated with dry mouth syndrome has been shown [14], the potential existence of individual genetic sensitivity to ^131^I in mediating the relationship between ^131^I exposure and salivary dysfunctions is important to study, especially as specific epigenetic changes could lead to increased sensitivity to ionizing radiation [15]. Other risk factors of salivary dysfunctions in the context of thyroid cancer treated by ^131^I-therapy are poorly understood. Only one study investigated the relationship between salivary flow and age, gender, or pathological tumor-node-metastasis (TNM) staging, but did not show any significant relationship, potentially owing to a lack of statistical power due to the small number of patients included (N=67) [11], emphasizing the importance of setting up a study with a large number of patients. Increased knowledge of these factors would help to identify the patients at risk of developing salivary dysfunctions, which could possibly help to adapt the treatment and follow-up accordingly.

In this context, the Salivary dysfuncTions After Radioiodine Treatment (START) study was launched in September 2020, with the following objectives: (1) to estimate the mid- and long-term incidence of salivary dysfunctions in patients with thyroid cancer treated with ^131^I, using objective, subjective, and mixed criteria; (2) to highlight risk factors of posttreatment salivary dysfunctions using clinical, pathological, biomolecular, and biochemical factors; (3) to validate a dosimetric method to calculate the dose absorbed by the salivary gland; (4) to estimate the dose-response relationship between exposure of the salivary glands to ^131^I and salivary dysfunctions; and (5) to investigate the consequences of salivary dysfunctions on the quality of life and nutritional status of patients.

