**Factor of interest**
Dose received by the salivary glands, administered dose

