**Adjustment factors to be tested**
Gender, self-rated menopausal status, age, BMI, histology, thyroid remnant tissue, pathological tumor-node-metastasis staging, thyroglobulin stimulation protocol, salivary comorbidities, medication intake, tobacco and alcohol consumption, surgery to therapy duration (months), family history of thyroid cancer

All statistical analyses will be performed using SAS statistical software for Windows (SAS Institute, Cary, NC). An α level of .05 will be accepted as significant.

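### Textbox 1 lists genetic and epigenetic variants only as outcomes of dose, contrary to the secondary endpoint of finding variants that modify the risk of dysfunction

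*Protocol article*

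**What the plan says.** Three parts of the Protocol article state the genetic aim with the variant as predictor or modifier:

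- Secondary Endpoints: "genetic and/or epigenetic variant identification that may modify the risk of salivary dysfunctions after ^131^I-therapy".
- Abstract, Methods: a plan to "search for potential biomarkers of the predisposition to develop salivary dysfunctions after ^131^I-therapy".
- Introduction: an interest in "individual genetic sensitivity to ^131^I in mediating the relationship between ^131^I exposure and salivary dysfunctions".

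Textbox 1, which summarises the planned analyses, assigns the roles differently:

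- Outcomes, continuous: the list ends with "mental composite score (MOS SF-36), genetic and/or epigenetic variants". The models and tests given for continuous outcomes are correlations, t test, linear regression and mixed model.
- Factor of interest: "Dose received by the salivary glands, administered dose", and nothing else.
- Adjustment factors to be tested: clinical and lifestyle items, ending with "salivary comorbidities, medication intake, tobacco and alcohol consumption, surgery to therapy duration (months), family history of thyroid cancer". No genetic or epigenetic term is listed.

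The paragraph that closes Statistical Analyses sets one significance level: "An α level of .05 will be accepted as significant".

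**The concern.** The stated aim and the stated model point in opposite directions. To learn whether a variant changes the risk of dysfunction, dysfunction must be the outcome and the variant a predictor. To learn whether the variant changes the effect of radiation, a variant-by-dose term is needed as well. Textbox 1 describes neither: read literally, it regresses the variant on dose.

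The article presents this as the first evaluation of variants involved in salivary dysfunction after radioiodine. Its Discussion expects the findings to help target patients at risk and possibly to adapt treatment. An analysis with the roles reversed could not support that use. A search judged at .05 for each variant would add chance findings, in a number that depends on how many variants are tested.

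**Working it through.** **Role of the variants.** No arithmetic applies here; the check is to set the passages side by side.

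| Source | Outcome | Explanatory side |
|---|---|---|
| Secondary Endpoints | dysfunction | variant, as a modifier of risk |
| Abstract, Methods | dysfunction | variant, as a predisposition marker |
| Introduction, rationale | dysfunction | dose, with genetic sensitivity |
| Textbox 1 | variant | dose, plus clinical covariates |

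Only Textbox 1 assigns variables to models, and it is the one that differs. An inherited genotype is fixed before treatment, so a coefficient of genotype on dose carries no information on who develops dysfunction.

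**Planned cases.** The article gives no figure for the genetic aim to reproduce; its sample size concerns the two activity groups. The Sample Size Calculation inputs (30% of 40 and 60% of 80) give 0.30 × 40 + 0.60 × 80 = 12 + 48 = 60 dysfunction cases.

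**False positives at .05.** The number of variants m is not stated and is assumed here. With independent tests and no true effect, expected false hits = 0.05 × m, and the chance of at least one = 1 − 0.95^m.

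| m (assumed) | Expected false hits | Chance of at least one |
|---|---|---|
| 20 | 1 | 64% |
| 100 | 5 | 99.4% |
| 1,000 | 50 | about 100% |

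**Share of hits that are false.** Let π be the share of tested variants truly associated. The false share is 0.05(1 − π) / [0.05(1 − π) + power × π]. It exceeds one half only when π < 0.05 / (0.05 + power):

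- power 80%: π below 5.9%
- power 50%: π below 9.1%
- power 30%: π below 14.3%

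For example, with π = 10% and power 80%, the false share is 0.045 / (0.045 + 0.080) = 36%. With π = 1% and the same power, it is 86%.

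**Power once variants are predictors.** Assume N = 120, half of the patients carriers, and dysfunction in 40% of non-carriers against 70% of carriers (66 cases, close to the planned 60). Power is approximately Φ[(0.30 − z × SE0) / SE1], where z is the two-sided critical value, SE0 = √(0.55 × 0.45 × 2/60) = 0.0908 and SE1 = √[(0.24 + 0.21)/60] = 0.0866.

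| Level | Power |
|---|---|
| 0.05 | 92% |
| 0.05/20 | 62% |
| 0.05/100 | 43% |
| 0.05/1,000 | 22% |

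These are Bonferroni levels; false discovery rate control would be somewhat less strict. If 20% of patients are carriers, power at 0.05/100 falls to 18%.

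**The case against.** Textbox 1 is a summary, and other text shows intent to test variants against dysfunction. The second objective names biomolecular factors among the risk factors. Planned Analyses describes a search for features shared by patients with dysfunction, then a 10% univariate screen into multivariate models. That stands as evidence of intent, so a reader should not infer that the aim is wholly absent from the plan. It does not remove the conflict: Planned Analyses refers to Textbox 1 for its models, the textbox lists no variant as a factor, and a univariate screen tests main effects, not modification.

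Epigenetic marks may legitimately respond to dose. Saliva is taken at T0 and T6, and Table 1 records variant data as proportions, which are quantitative. This stands in full; the objection to variants as outcomes applies to inherited variants.

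The endpoint wording can be read as simple association with risk among treated patients, so an interaction is not clearly promised. This also stands, and is why the variant-by-dose term is proposed as exploratory only.

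On multiplicity, a reader might infer that correction has been ruled out, or that most hits would be false. The documents support neither. A general .05 level does not forbid adjustment, and an analysis plan that is not shown may specify it. Whether false hits form the majority depends on the number of variants and the share truly associated, and neither is given. A wide screen makes it likely; a short candidate list may not.

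**Conclusion.** The contradiction holds. As specified in Textbox 1, the analysis cannot answer the secondary endpoint for inherited variants, and the passages must be reconciled. This conclusion rests on the text alone and needs no numerical assumption.

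The multiplicity point is secondary and conditional. The single .05 level carries no exception for the variant search, but the size of the problem is known only as a range under the assumption of independent, all-null tests. The point concerns one secondary endpoint and leaves the primary endpoint untouched.

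**What to change.** 1. In Textbox 1, list variants as explanatory factors in the models of dysfunction at T6 and T18, adjusted for gland dose and the other chosen covariates.
2. Add a variant-by-dose term as an exploratory test of effect modification.
3. Keep epigenetic change from T0 to T6 as a separate outcome with dose as the factor, and remove inherited variants from the outcome list.
4. State the number of variants to be tested, control the false discovery rate across them (for example Benjamini–Hochberg at 5%), and report those that pass as candidates needing replication.

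This changes analysis wording only and needs no new data. The price is power: with about 60 planned cases, only large main effects would survive correction over 100 or more variants, and the interaction test would generally have less power still.

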**Models and tests**
Categorical*χ*^2^, logistic regression, Poisson regressionContinuousCorrelations, *t* test, linear regressions, mixed model
**Factor of interest**
Dose received by the salivary glands, administered dose
**Adjustment factors to be tested**
Gender, self-rated menopausal status, age, BMI, histology, thyroid remnant tissue, pathological tumor-node-metastasis staging, thyroglobulin stimulation protocol, salivary comorbidities, medication intake, tobacco and alcohol consumption, surgery to therapy duration (months), family history of thyroid cancer

All statistical analyses will be performed using SAS statistical software for Windows (SAS Institute, Cary, NC). An α level of .05 will be accepted as significant.

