Salivary dysfunctions may lead to an increased risk of inflammation and/or oral infection, a change in the taste of food, and difficulties in swallowing and digestion. Lacrimal gland dysfunctions (one of the diagnostic criteria for Sjögren syndrome) have also been reported after ^131^I-therapy, suggesting that some patients may develop simultaneous lacrimal and salivary gland dysfunctions in the years following ^131^I-therapy [7]. Quality of life after ^131^I-therapy requires special attention because of the good prognosis of differentiated thyroid cancer. In the context of ^131^I-therapy for thyroid cancer, few studies have assessed the long-term quality of life at 6 months or later after ^131^I-therapy [8-12], whereas it has been shown that salivary dysfunction assessed by a specific questionnaire may occur more than 6 months after therapy for 25% of patients [13]. Moreover, there are inconsistencies in the reported relationships between objective measures of salivary flow (sialometry) and subjective measures of salivary dysfunction (self-questionnaire) [6,11], reinforcing the need to assess salivary dysfunction by creating a composite criterion combining objective and subjective measures.

Additionally, the dose-response relationships between ^131^I-therapy and the incidence of salivary and lachrymal dysfunctions have been rarely studied, and the administered activity is typically used as a proxy for the dose absorbed by the salivary glands. However, the administered activity does not accurately reflect the dose received by the salivary glands due to the variation in iodine uptake ability of the salivary gland, which could be modified by the size of the thyroid remnant tissues or a potential iodine deficiency of the patient before treatment, along with the inherent interpatient variability affecting the entire biokinetics of iodine. The use of an adapted dosimetric method using thermoluminescent dosimeters and anthropomorphic phantoms would make it possible to better estimate the dose-response relationship by estimating the absorbed dose to the salivary gland.

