### Data Collection

All data are collected using paper versions, and are then entered and recorded on a secure server (Table 1).

All questionnaires are completed at each measuring point of the study for each patient. Questionnaires have been selected on the basis of ease and speed of administration by an interviewer, peer-validated, and on the fact that they are the most widely used questionnaires in this type of research (see Multimedia Appendix 1).

Saliva sampling has been performed according to a standardized methodology (see Multimedia Appendix 2).

**Table 1 table1:** Summary of data collection.

Data type	Qualitative data	Quantitative data
Thyroid cancer information (collected only at the enrollment visit)	Size of the postsurgery remnant, tumor histology, pTNM^a^ staging, Tg^b^ stimulation protocol, family history of thyroid cancer, patient history of cancer or comorbidities, prescribed activity of ^131^I (1.1 or 3.7 GBq)	Surgery to therapy duration (months)
Clinical data	Self-rated menopausal status, all medications used during the last 3 months, tobacco and alcohol consumption, self-palpation of the salivary glands (normal, painful, or swollen), self-reported oral carries or infections, observed cracked lips, self-reported use of a saliva substitute, sialagogue	Age, height, weight
Questionnaires	Salivary complaints questionnaire; eye dryness, OSDI^c^ questionnaire; questions about nutrition; anxiety and depressive symptoms (HAD^d^ scale)	Physical and mental composite scores about quality of life (MOS SF-36^e^)
Saliva samples	Not applicable	Weight (precision 0.01 mg), volume (precision 0.01 mL), electrolyte concentrations (mmol/L: sodium, potassium, chloride, amylase, and total protein composition), genetic and epigenetic variant proportions

^a^pTNM: pathological tumor-node-metastasis.

^b^Tg: thyroglobulin.

^c^OSDI: Ocular Surface Disease Index.

^d^HAD: Hospital Anxiety and Depression.

^e^MOS SF-36: Medical Outcome Study Short Form 36 items.

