### Study Endpoints

#### Primary Endpoint

The primary endpoint is a composite criterion combining objective (salivary flow dysfunctions with and/or without stimulation) and subjective (reporting discomfort, pain in the parotid area, difficulty swallowing, or eye dryness) criteria at T6. Salivary flow dysfunctions are defined as an unstimulated salivary flow <0.2 mL/min and/or a stimulated salivary flow <0.7 mL/min [18,19].

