## Results

Patient enrollment took place from September 2020 to April 2021, with a total of 139 patients enrolled, including 45 and 94 patients treated with 1.1 and 3.7 GBq ^131^I, respectively.

Characteristics of the study participants are displayed in Table 2. The START sample is composed of a large majority of women, with an average age of 47 years (range 18.70-81.80 years). All patients underwent total thyroidectomy with a diagnosis of differentiated thyroid cancer confirmed by pathological examination; the highest proportion in the TNM classification was Tx-T2, followed by Nx-N0, N1, T3, and T4, including approximately 47% of patients with residual thyroid tissue. The ^131^I-therapy was performed an average 4.11 (SD 3.91) months after the surgery (range 1-35 months). The majority of the included patients were treated for a papillary thyroid cancer.

Concerning the saliva samples, the mean pH was 7.34 (SD 0.48; range 6.00-8.50), with flow rates of 0.76 (SD 0.46; range 0.04-3.00) mL/min and 2.13 (SD 0.88; range 0.40-4.82) mL/min for unstimulated and stimulated saliva, respectively.

Statistically significant differences between the 1.1 and 3.7 GBq treated groups were found in saliva pH and nonstimulated saliva volume.

At the enrollment visit, among all 139 patients, 19 (13.6%) patients had suspicious or obvious symptoms of depression, whereas 67 (48.2%) patients had suspicious or obvious symptoms of anxiety according to the Hospital Anxiety Depression scale (see Table S1 in Multimedia Appendix 3).

When asked if patients experienced changes after thyroid removal surgery, 25 (18.0%) had the sensation of a dry mouth, 48 (34.5%) said they drink more often, and 27 (19.4%) were eating less salty foods.

Regarding lifestyle habits, among the 139 patients, 95 (68.3%) had never smoked, compared to 28 (20.1%) exsmokers and 16 (11.5%) current smokers; 87 (62.6%) never drink alcohol, compared to 45 (32.4%) being occasional drinkers (1-7 drinks/week) and 7 (5.0%) being regular drinkers (7-14 drinks/week) (see Table S1 in Multimedia Appendix 3).

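### The printed adjustment list omits baseline HAD anxiety and depression, leaving T0 mood as a possible common cause of reported salivary dysfunction and reported quality of life in objective 5

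*Protocol article*

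**What the plan says.** - **Adjustment factors (Planned Analyses, Textbox 1).** The list opens with gender, menopausal status, age, BMI, histology, remnant tissue, staging and stimulation protocol. It closes with "salivary comorbidities, medication intake, tobacco and alcohol consumption, surgery to therapy duration (months), family history of thyroid cancer". No anxiety, depression or HAD term appears.
- **Role of HAD (same textbox).** Both HAD scales stand among the categorical outcomes. The factors of interest are gland dose and administered dose.
- **Model building (Planned Analyses).** Factors that pass a 10% univariate screen enter the multivariate models. Mixed models carry a random intercept per patient and are said to be adjusted for confounders, which are not named there.
- **Timing (Data Collection; Enrollment Visit).** "All questionnaires are completed at each measuring point of the study for each patient". The T0 visit takes place on the treatment day, before the capsule is given.
- **Frequency at T0 (Results).** "67 (48.2%) patients had suspicious or obvious symptoms of anxiety according to the Hospital Anxiety Depression scale", and "19 (13.6%) patients had suspicious or obvious symptoms of depression".
- **Primary endpoint.** One component is measured: "Salivary flow dysfunctions are defined as an unstimulated salivary flow <0.2 mL/min and/or a stimulated salivary flow <0.7 mL/min". The other is reported by the patient: "subjective (reporting discomfort, pain in the parotid area, difficulty swallowing, or eye dryness) criteria at T6". How the two are combined is not stated.
- **Objective 5 (Introduction).** It concerns the consequences of salivary dysfunction for quality of life and nutrition. The quality-of-life endpoint is change between T0, T6 and T18.

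**The concern.** In objective 5 the exposure (dysfunction, in part a complaint) and the outcome (SF-36) are both reported by the same patient. A patient who is anxious before treatment may be more likely to report discomfort, pain or dryness at T6, and may also score lower on quality of life. That would produce an association between dysfunction and quality of life that does not come from the glands. The Introduction itself acknowledges "inconsistencies in the reported relationships between objective measures of salivary flow (sialometry) and subjective measures of salivary dysfunction", and reporting tendency is one plausible reason for such disagreement. No listed factor represents it directly; medication intake is at best a weak proxy.

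T0 HAD is measured before exposure, so it cannot be a consequence of radioiodine and may properly be adjusted for. A factor absent from the list of factors to be tested would not reach the univariate screen, and so would not enter the logistic or Poisson models of T6 outcomes.

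**Working it through.** **Inputs**
- From the article: T0 anxiety 67/139 = 0.482, as printed. T0 depression 19/139 = 0.137 (printed 13.6%).
- Assumed, because the article gives no figures: dysfunction in 40% of patients not anxious at T0; odds ratio (OR) for dysfunction if anxious 1.5 to 3; mental score 5 to 10 points lower if anxious; no true effect of dysfunction on quality of life.

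**Step 1: T6 levels.** Spurious gap = D × [P(anxious | dysfunction) − P(anxious | none)], where D is the mood gap in score.
- OR 1.5: odds 0.667 × 1.5 = 1.0, so 50% of anxious patients have dysfunction. P(dysfunction) = 0.482 × 0.50 + 0.518 × 0.40 = 0.448. P(anxious | dysfunction) = 0.241/0.448 = 0.538; P(anxious | none) = 0.241/0.552 = 0.437. The difference is 0.101, and × 5 points gives **0.50**.
- OR 3: odds 2.0, so 66.7%. P(dysfunction) = 0.321 + 0.207 = 0.529. The conditional probabilities are 0.608 and 0.341. The difference is 0.267, and × 10 points gives **2.67**.

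A cross-check on complaints alone, with complaint rates of 25% if not anxious and 40 to 50% if anxious, gives 0.86 to 2.68 points. In either calculation the gap vanishes within strata of T0 anxiety.

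**Step 2: dilution in the composite.** Mood acts on the complaint component. Assume 20% flow dysfunction, 25% complaints without anxiety and an either-component rule.
- Complaint OR 1.5: complaints 33.3%, composite 1 − 0.8 × 0.667 = 46.7% against 40.0%. The composite OR is 0.875/0.667 = 1.31, and the gap at 5 points is 0.34.
- Complaint OR 3: complaints 50%, composite 60%. The composite OR is 1.5/0.667 = 2.25, and the gap at 10 points is 2.00.

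The T6-level range for the composite would then be about 0.3 to 2.0 points.

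**Step 3: change from T0.** The gap in change is (D at T6 − D at T0) × 0.101 to 0.267. If the mood gap is the same at both visits, this is 0. Each point by which the mood gap alters between visits adds 0.10 to 0.27 points. The sign is open: if anxiety on the treatment day partly subsides by T6, anxious patients improve more, and the bias runs the other way.

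**Step 4: activity contrast.** Keep the Step 2 flow and complaint inputs with complaints of 40 to 50% if anxious, the either-component rule and no true dose effect. The false OR between the 3.7 and 1.1 GBq groups is 1.00 if anxiety is balanced, 1.05 to 1.08 if it differs by 10 percentage points, and 1.10 to 1.17 if it differs by 20. The article's shown text does not give the actual difference.

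**The case against.** **The design is self-controlled.** Quality of life is analysed as change from T0, with paired comparisons and random intercepts. This is the strongest reply, and it largely stands: Step 3 shows that a stable mood gap cancels in a change score. It does not dispose of the point. A random intercept does not remove confounding between two patient-level characteristics, here T0 mood and dysfunction status at T6. Mood may also predict change itself.

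**The list is a synthesis of factors to be tested, and a fuller plan may add to it.** This is fair as far as it goes. But the list is explicit, goes down to family history and surgery-to-therapy delay, and gives HAD another role.

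**T0 HAD is an imperfect measure of reporting tendency.** It is taken on the treatment day, when 25 patients (18.0%) already had a dry-mouth sensation, and 52% of the 3.7 GBq group but none of the 1.1 GBq group had stopped L-thyroxine. It may therefore reflect a passing state or existing symptoms. The patient's own T0 complaint is the more direct control. This stands, and the fix includes it.

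**Flow-only analysis is partly foreseen.** Objective 1 names objective, subjective and mixed criteria. Objective 5, however, does not say which criterion it uses.

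**A stronger reading.** A reader might infer that complaint-prone patients distort the dose-response or the 1.1 versus 3.7 GBq comparison. The documents do not support this. T0 mood confounds those contrasts only if it varies with dose, and HAD by group is not shown.

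**Conclusion.** The omission is real and its demonstrated consequence is limited. T0 HAD is measured before radioiodine, anxiety symptoms are frequent at T0 (depression symptoms much less so), and the printed list leaves both out. What remains is possible residual confounding in objective 5, and some loss of precision in the T6 subjective and composite models from leaving out a plausible predictor.

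The 0.5 to 2.7 points apply to a T6-level comparison and rest on assumed values for everything except the 48.2%. For change from T0 the bias is much smaller and may be nil. The effect on the composite also depends on the unstated combination rule: with the Step 2 inputs and complaints of 40 to 50% if anxious, the overall rate moves from 40.0% to 45.8–49.6% under an either-component rule, but only from 5.0% to 6.4–7.4% if both are required.

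A reader might take those rates to mean that adjustment would correct the incidence estimate. It would not; that calls for reporting the objective and subjective components separately, which objective 1 already foresees.

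**What to change.** 1. In the objective 5 models, and in the T6 models of the subjective criterion and the composite, enter the T0 HAD anxiety and depression scores as continuous covariates, whatever the result of the 10% screen.
2. In the same models, enter the patient's own T0 value of the outcome: the T0 complaint for the subjective and composite models, the T0 SF-36 score for quality of life.
3. Do not adjust for T6 HAD. It is a study outcome and may be a consequence of dysfunction.
4. Report objective 5 also with dysfunction defined by salivary flow alone, so that the exposure is not self-reported.
5. Tabulate T0 HAD by activity group alongside the dose-response results, so that readers can judge whether mood varies with dose.

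In logistic models the adjusted odds ratio can shift without any confounding, so a shift alone should not be read as proof of it.

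Cost: a few degrees of freedom per model (two HAD scores and one baseline value), one sensitivity analysis and one table. All the data are already collected, and the sample size is unaffected.
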